### Interventions {11a}

Upon obtaining signed informed consent from the subject, the following process is executed (Figs. 2 and 3):Screening periodAfter the patient enters the endoscopy examination room and decides to undergo upper gastrointestinal endoscopy treatment, the researcher collects information on the patient’s demographics, medical condition, and proposed examination plan. An independent anesthesiologist evaluates the patient’s examination plan before randomization, and eligible patients are selected based on the inclusion/exclusion criteria. Patients should be assessed by researchers who are knowledgeable about the protocol and authorized to do so in a quiet environment. The study’s purpose, methods, potential benefits, and risks must be thoroughly explained to the patient and/or their representative, and data collection and follow-up procedures before, during, and after the examination must be detailed.The researchers should address the patient and their family members’ questions in detail, allowing sufficient time for consideration and obtaining informed consent from the patient and/or their representative on a completely voluntary basis. The assessor must not be involved in the patient’s examination, sedation, or anesthesia management plan. *Sedation management plan*: An anesthetist with the title of attending physician or above will implement the sedation and anesthesia plan. The patient enters the endoscopy consultation room’s preparation area and takes 10 g of lidocaine gel (containing 0.2 g of lidocaine) orally 5 min before the examination. The patient assumes a left lateral position on the treatment bed in the endoscopy consultation room, and basic vital signs including noninvasive blood pressure (NIBP) of the right upper arm, electrocardiogram, and pulse oxygen saturation (SpO_2_) are monitored. Oxygen is continuously administered through a 4L/min nasal cannula throughout the procedure until the patient fully awakens. A venous line is established, and sufentanil 5 μg is administered intravenously. Patients scheduled for upper gastrointestinal endoscopy are randomized to receive one of two sedative drug infusions: propofol in group C or remimazolam in group R. In group C, patients receive a single dose of propofol at 1.5 mg/kg, while in group R, patients receive a single dose of remimazolam at 0.15 mg/kg, both administered within 1 min. According to the domestic expert consensus, moderate or deep sedation is required for upper gastrointestinal endoscopic examination. Therefore, the MOAA/S score (Appendix 2) should be assessed 1 min after propofol injection. If the MOAA/S score is greater than 3 points, propofol 0.5 mg/kg or remimazolam 0.05 mg/kg should be administered repeatedly until the MOAA/S score is less than or equal to 3 points, with a maximum of five repetitions. The VAS (Appendix 3) should be assessed during propofol or remimazolam injection.*Intraoperative monitoring*: Intraoperative monitoring includes electrocardiogram, noninvasive blood pressure, pulse oxygen saturation, and, when necessary, body temperature, urine output, end-tidal carbon dioxide concentration, and blood glucose levels.*Sedation maintenance plan*: During the examination procedure, the chief anesthesiologist determines whether to administer additional trial medication based on the surgical process and duration. Propofol (0.5 mg/kg) or remimazolam (0.05 mg/kg) is administered in single doses with a minimum interval of 1 min to maintain the patient at an appropriate level of sedation (MOAA/S score ≤ 3). If sedatives are insufficient to maintain appropriate sedation during the examination, the investigator may decide to use alternative sedative agents (midazolam).*Examination plan*: Based on the type of lesion, the endoscopic examination of the upper digestive tract in our hospital may include, but is not limited to, upper gastrointestinal inflammation, tumors, ulcers, polyps, gastroesophageal varices, and gastrointestinal strictures. According to the type of endoscopic treatment of the upper gastrointestinal tract, it may include, but is not limited to, sclerotherapy, argon plasma coagulation, high-frequency electrocautery, and submucosal dissection. Various procedures are conducted following established clinical surgical protocols. *Postoperative management plan*: After the examination or procedure, the patient enters the anesthesia recovery room, where continuous monitoring of ECG, noninvasive blood pressure, and oxygen saturation occurs. The MOAA/S score is assessed every 5 min. Once the score reaches 5 points for three consecutive assessments, and blood pressure, heart rate, and oxygen saturation are normal and stable, the patient can leave the recovery room accompanied by a companion. In case of special circumstances, refer to the adverse event handling procedures.

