#### Recovery room data collection

Immediately after the examination, the patient is transported to the recovery room until fully awake.

After entering the recovery room, test the MOAA/S score every 5 min and record it.

Record the time required from the end of the operation to the patient’s MOAA/S score recovering to 5 points (need to reach 5 points continuously for three times, choose the first time with a score of 5).

Measure NIBP every 3 min after entering the recovery room and record it.

Continuously monitor SpO_2_ until the end of the examination and record the minimum SpO_2_ during the procedure.

Adverse events occurring in the recovery room (see 1.10), such as SpO_2_ below 90%, positive pressure mask ventilation, jaw support-assisted ventilation, systolic blood pressure < 80 mmHg or the need for vasopressors, systolic blood pressure ≥180 mmHg, *HR* ≤ 55 beats/min, and *HR* > 100 beats/min

When the subjects meet the discharge criteria, record their anesthesia satisfaction score (0–10 points, with 0 indicating very dissatisfied and 10 indicating very satisfied).

Whether flumazenil was used for antagonism in case of delayed awakening.

When the patient’s MOAA/S score recovers to 5 points, use the modified Brice questionnaire to determine if the patient was aware during the procedure.

Collect information on the operator’s years of experience.

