#### Secondary outcomes

*Sedation efficacy outcomes*: (1) MOAA/S score after single administration; (2) time required to achieve a MOAA/S score of ≤ 3 points following single administration; (3) for patients not achieving adequate sedation depth after a single dose and documentation of additional medication doses and frequency; (4) total amount and number of additional administrations of remimazolam or propofol in both groups during the entire course of upper gastrointestinal endoscopy and treatment; (5) duration from the initiation of medication injection to the completion of upper gastrointestinal endoscopy and treatment; (6) type, frequency, and dose of alternative or additional remedial drugs required when the upper limit of supplementary dosage is exceeded; and (7) operator satisfaction.

*Consciousness recovery outcomes*: (1) Time to full awakening; (2) use of sedative antagonist flumazenil, if applicable; (3) assessment of patients’ recall of upper gastrointestinal endoscopy and treatment process using the Brice questionnaire (Appendix 4) after awakening; (4) duration of patients’ recovery; and (5) overall patient satisfaction.

*Safety outcomes*: (1) Incidence of hypertension or hypotension during the procedure and in the recovery room, (2) incidence of tachycardia or bradycardia during the procedure and in the recovery room, (3) incidence of low oxygen saturation during the procedure and in the recovery room, (4) airway intervention rate during the procedure and in the recovery room, (5) incidence of coughing within 1 min after endoscope insertion, (6) incidence of coughing during upper gastrointestinal endoscopy and treatment, and (7) incidence of injection-related pain.

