#### Efficacy evaluation{20a}

Primary endpoint evaluation: In the intention-to-treat (ITT) analysis population, a chi-square test will be used to compare the success rates of patients completing endoscopic examination and treatment between the two groups. Simultaneously, a generalized linear model will be employed to calculate the unadjusted and adjusted absolute risk differences (ARD). Adjusted variables will encompass stratification indicators (invasive procedures during upper gastrointestinal endoscopy and treatment), BMI, age, concurrent respiratory diseases, concurrent cardiovascular and cerebrovascular diseases, liver and kidney function abnormalities, and operator experience. Secondary effect sizes will be presented as odds ratios (OR) with a 95% confidence interval.

Evaluation of secondary endpoints: For the intention to treat (ITT, includes all participants who were randomly assigned, regardless of whether they completed the entire study or fully adhered to the study protocol) population, chi-square test or *t*-test will be employed for comparative analysis based on variable nature (e.g., categorical variables like low oxygen saturation, hypotension, tachycardia, intraoperative awareness, recovery delay, or continuous variables such as MOAA/S, NIBP, HR, and SpO_2_). Results will be reported as odds ratios (OR) and 95% confidence intervals using a generalized linear model. Time event variables (e.g., time to achieve a MOAA/S score of ≤ 3 points after a single dose) will be analyzed using Cox regression to describe and compare the two groups, generate Kaplan-Meier curves, express results as hazard ratios (HR), and report a 95% confidence interval.

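### Safety outcomes 1 to 4 count recovery-room events over a stay that ends on waking, so any difference in waking time between arms would make observation unequal; a common-window comparison should be added.

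*Protocol article*

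**What the plan says.** All references are to the protocol article.

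- **Outcome.** Under Secondary outcomes, safety outcome 1 is "Incidence of hypertension or hypotension during the procedure and in the recovery room" and outcome 3 is "incidence of low oxygen saturation during the procedure and in the recovery room". Outcomes 2 (tachycardia or bradycardia) and 4 (airway intervention) cover the same two periods.
- **End of observation.** Under Recovery room data collection: "Immediately after the examination, the patient is transported to the recovery room until fully awake". The postoperative plan in Interventions {11a} lets the patient leave under this condition: "Once the score reaches 5 points for three consecutive assessments, and blood pressure, heart rate, and oxygen saturation are normal and stable".
- **Intensity of measurement.** In the recovery room, "The MOAA/S score is assessed every 5 min", and the data collection section adds "Measure NIBP every 3 min after entering the recovery room and record it".
- **Analysis.** For secondary endpoints, Efficacy evaluation {20a} says "chi-square test or *t*-test will be employed for comparative analysis based on variable nature". It names low oxygen saturation, hypotension and tachycardia among the categorical variables and reports odds ratios. It states no common window and no allowance for observation time.
- **Waking.** Time to full awakening and duration of recovery are themselves secondary outcomes.
- **After leaving.** The only later contact is a telephone call on day 1.

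**The concern.** The stay ends on an event, waking, that the study drug may influence. A patient who wakes later is watched for longer and has more 3-minute pressure readings, so there are more chances to cross a threshold such as systolic pressure of 180 mmHg or more, or heart rate above 100. The telephone call cannot recover such readings for patients who have already left. A plain proportion over the stay therefore mixes the risk of an event with the time spent looking for it. If waking times differ, the faster-waking drug could look safer in the recovery room partly because monitoring stopped sooner. Safety is a stated aim of the trial, so the recovery-room comparison is one that readers will use.

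**Working it through.** **Plan's own figures.** The protocol gives no expected incidence or length of stay for the recovery room, so there is no figure on this point to reproduce. Its sample size does reproduce: (1.96 + 0.84)² × 2 × 0.79 × 0.21 / 0.10² gives 261 per arm, 522 in all, and 261 × 1.1 rounds up to 288 per arm, 576 in all. The 288 is used in step 4.

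**Inputs from the protocol.** MOAA/S every 5 min in recovery; exit after three consecutive scores of 5; NIBP every 3 min. Two gaps of 5 min make the shortest rule-compliant stay 10 min, and more generally the stay is at least the time of the first score of 5 plus 10 min.

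**Assumptions.** Stays of 15 v 20 min (also 15 v 25 min), the same event risk in both arms, and the hazards shown below.

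**1. Recovery room only, constant hazard h per minute.** Incidence = 1 − exp(−hT).

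| h per min | 15 min | 20 min | OR, 15 v 20 | OR, 15 v 25 |
|---|---|---|---|---|
| 0.3% | 4.4% | 5.8% | 1.34 | 1.69 |
| 0.5% | 7.2% | 9.5% | 1.35 | 1.71 |
| 1.0% | 13.9% | 18.1% | 1.37 | 1.76 |

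**2. Recovery room only, falling hazard.** With half-life L and k = ln 2 / L, incidence = 1 − exp[−(h₀/k)(1 − exp(−kT))]. For 15 v 20 min the OR is about 1.02 at L = 3 min and 1.07 to 1.08 at L = 5 min. For 15 v 25 min it runs from about 1.03 to 1.12. The extra minutes come when little hazard is left.

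**3. Procedure plus recovery room, constant hazard.** This is the quantity the protocol defines. With the same procedure risk r in both arms, incidence = 1 − (1 − r)exp(−hT). For 15 v 20 min and h from 0.3% to 1.0%, the OR is 1.16 to 1.28 at r = 5%, and 1.08 to 1.23 over r = 10% to 15%.

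**4. Second model: risk q per NIBP reading.** Incidence = 1 − (1 − q)^k, where k is the number of whole 3-minute intervals in the stay. The last column is the chance of p < 0.05 with 288 per arm (normal approximation) as q runs from 0.5% to 2%.

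| First MOAA/S 5 (assumed) | Recovery readings | OR | Chance of p < 0.05 |
|---|---|---|---|
| 5 v 5 min | 5 v 5 | 1.00 | 5% |
| 5 v 10 min | 5 v 6 | about 1.2 | 6–11% |
| 5 v 15 min | 5 v 8 | about 1.6 | 17–49% |

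Example at q = 1%, 5 v 8 readings: 4.9% v 7.7%, OR 1.62, chance 29%. Adding an assumed 10-min procedure to the 5 v 15 min case gives 8 v 11 readings, OR about 1.4 and a chance of 13–35%.

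**5. Common window.** With equal observation in both arms, equal risk gives equal incidence, OR 1.00 and the nominal 5%.

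**The case against.** The strongest defence is that whole-stay incidence is a legitimate randomised comparison. The proportion of patients who desaturate or become hypotensive before leaving monitored care is a real clinical quantity, and if one drug prolongs sedation and more patients have events as a result, that is a drug effect. This stands, and it is why the whole-stay comparison should be kept. It does not make the whole-stay figure a comparison over equal time, because measurement stops at different points.

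A reader might infer that the trial expects the drugs to differ in waking speed, so that the slower arm must show more events. The document does not support that. No section predicts a remimazolam–propofol difference; the Background credits propofol with rapid recovery and sets remimazolam's half-life against midazolam's. An excess follows only if stays differ and risk per minute is equal; a lower hazard in the slower arm could offset it. Nor should 1.34 to 1.76 be read as the expected distortion, since those values omit the procedure period and assume a constant hazard.

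Some of this is visible elsewhere in the plan. Recovery times are reported by arm, and the exploratory mixed model for repeated readings evaluates a group-by-time interaction. Neither turns the threshold-event incidences into a comparison over equal time. The choice of chi-square test and odds ratio is written in the protocol, so it is not simply a detail left to an analysis plan.

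**Conclusion.** The point holds in a limited form. The observation period for safety outcomes 1 to 4 can depend on treatment through waking time, and the stated analysis does not separate event risk from time observed. Direction and size are unknown, because the protocol gives no expected stay by arm. If stays are alike, the distortion is close to nil. For a 5-minute difference in stay at equal risk, the recovery-room odds ratio lies between about 1.02 and 1.37 depending on how fast the hazard falls, and at about 1.1 to 1.3 once procedure events are included at constant hazard. A 10-minute difference at constant hazard would matter more.

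A reader might extend this to the non-inferiority result. That does not follow: the primary composite counts oxygen saturation, blood pressure and heart rate events during the examination only, so the primary test and the sample size are unaffected.

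**What to change.** 1. Report procedure and recovery-room incidences separately for safety outcomes 1 to 4.
2. Add a between-arm recovery-room comparison over the first 10 min after entry. Every patient who follows the stated exit rule completes this window.
3. Keep the whole-stay comparison beside it, shown with length of stay by arm.
4. Do not analyse the whole stay as a rate with log minutes as offset. Leaving requires stable vital signs, so an event can lengthen the stay and inflate its own denominator.
5. Reconcile the SpO2 wording: the recovery-room data list runs monitoring to the end of the examination, whereas Interventions {11a} has it continuing in the recovery room.

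The cost is one more analysis and some wording. Recovery NIBP and MOAA/S values are already recorded, and Safety and adverse events {22} puts event times on the CRF. Analysis is scheduled only at the end of the study, so the change can be written in beforehand. The downside is small: the common window does not cover events after 10 min, which may include harms of prolonged sedation, but these remain in the whole-stay comparison.

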### Sample-size calculation {14}

The study plans to enroll 576 patients. The basis for sample size calculation is as follows: According to the literature report [7], patients undergoing upper gastrointestinal endoscopy and treatment with propofol sedation had a completion rate without sedation-related complications of 79%. Using a two-sample *z*-test for proportions to assess the primary outcome measure, the estimated non-inferiority margin is an absolute difference of 10% for the primary outcome measure. Setting a non-inferiority difference value of 0.1, a power (1-β) of 0.8, and a one-sided α of 0.025, a total sample size of 522 cases is required for the calculation. Accounting for an anticipated loss to follow-up rate of 10%, the total sample size is 576 cases (288 participants per group).

### Recruitment {15}

The principal method involves a collaborative partnership with the Endoscopy Center of the Second People’s Hospital of Futian District, Shenzhen, serving as a centralized hub for participant enrollment. Furthermore, we have employed a range of strategies, including in-person invitations during clinical visits and referrals from physicians across various medical disciplines. Designated personnel from this department will be responsible for identifying and enrolling eligible participants who meet the inclusion criteria. The confidential information of the participants will be securely stored within the Clinical Trial Public Management Platform (ResMan) and will not be disclosed to any individuals or organizations unrelated to this study.

### Statistical analysis

#### General principles{20a}

Continuous variables will be represented as means (standard deviations) or medians (minimum, maximum, or interquartile range), with the Shapiro-Wilk test applied to evaluate the normality of continuous variable distributions. Categorical variables will be expressed as frequencies (percentages).

All statistical analyses will involve two-sided tests, considering a *p*-value less than 0.05 to be statistically significant.

#### Patient recruitment and withdrawal status

The enrollment and attrition of patients will be documented.

#### Demographic and baseline characteristics

Demographic data and baseline characteristics, such as preoperative comorbidities and medication history, will be presented.

#### Efficacy evaluation{20a}

Primary endpoint evaluation: In the intention-to-treat (ITT) analysis population, a chi-square test will be used to compare the success rates of patients completing endoscopic examination and treatment between the two groups. Simultaneously, a generalized linear model will be employed to calculate the unadjusted and adjusted absolute risk differences (ARD). Adjusted variables will encompass stratification indicators (invasive procedures during upper gastrointestinal endoscopy and treatment), BMI, age, concurrent respiratory diseases, concurrent cardiovascular and cerebrovascular diseases, liver and kidney function abnormalities, and operator experience. Secondary effect sizes will be presented as odds ratios (OR) with a 95% confidence interval.

Evaluation of secondary endpoints: For the intention to treat (ITT, includes all participants who were randomly assigned, regardless of whether they completed the entire study or fully adhered to the study protocol) population, chi-square test or *t*-test will be employed for comparative analysis based on variable nature (e.g., categorical variables like low oxygen saturation, hypotension, tachycardia, intraoperative awareness, recovery delay, or continuous variables such as MOAA/S, NIBP, HR, and SpO_2_). Results will be reported as odds ratios (OR) and 95% confidence intervals using a generalized linear model. Time event variables (e.g., time to achieve a MOAA/S score of ≤ 3 points after a single dose) will be analyzed using Cox regression to describe and compare the two groups, generate Kaplan-Meier curves, express results as hazard ratios (HR), and report a 95% confidence interval.

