**Methods:**

A total of 576 high-risk patients scheduled to undergo upper gastrointestinal endoscopy are planned to be enrolled in this study and randomly allocated to either the remimazolam or propofol group. The primary outcome measure is a composite endpoint, which includes (1) achieving a Modified Observer’s Alertness/Sedation scale (MOAA/S) score ≤ 3 before endoscope insertion, (2) successful completion of the endoscopic procedure, (3) the absence of significant respiratory instability during the endoscopy and treatment, and (4) the absence of significant circulatory instability during the examination. The noninferiority margin was 10%. Any adverse events (AEs) that occur will be reported.

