## Methods/design

### Trial design {8}

We have developed a single-center, randomized, parallel group controlled, non-inferiority trial to compare the sedative effects of remimazolam and propofol in high-risk populations undergoing upper gastrointestinal endoscopy. A total of 576 high-risk patients scheduled for upper gastrointestinal endoscopy will be enrolled and randomly allocated to either the remimazolam group or the propofol group using a block randomization method (Fig. 1). This study adheres to the principles of Good Clinical Practice for Drug Trials, in accordance with the Declaration of Helsinki. The SPIRIT checklist is provided in Additional file 1.

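### The test named for the primary endpoint is a two-sided test of equality that never uses the 10-point margin, so it cannot show non-inferiority

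*Protocol article*

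**What the plan says.** Trial design {8} calls the study a "single-center, randomized, parallel group controlled, non-inferiority trial". Sample-size calculation {14} states that "the estimated non-inferiority margin is an absolute difference of 10% for the primary outcome measure". It names the test ("Using a two-sample *z*-test for proportions to assess the primary outcome measure") and the operating characteristics: "Setting a non-inferiority difference value of 0.1, a power (1-β) of 0.8, and a one-sided α of 0.025".

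The analysis section reads differently. General principles {20a} states: "All statistical analyses will involve two-sided tests", with significance at p < 0.05 and no exception for the primary endpoint. Efficacy evaluation {20a} says that, in the intention-to-treat population, "a chi-square test will be used to compare the success rates of patients completing endoscopic examination and treatment between the two groups". It adds risk differences from a generalized linear model, with and without covariate adjustment, and then: "Secondary effect sizes will be presented as odds ratios (OR) with a 95% confidence interval".

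From General principles to Sensitivity analysis {20c}, neither the margin nor a rule for declaring non-inferiority is mentioned.

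**The concern.** A chi-square test of two success rates has equality as its null hypothesis. The trial's null hypothesis is that remimazolam is worse than propofol by 10 points or more. The p-value for the first says little about the second:

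- p above 0.05 is compatible both with non-inferiority and with a deficit larger than the margin.
- p below 0.05 does not by itself refute non-inferiority, because the difference may favour remimazolam.

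The only interval named for the primary endpoint is on the odds ratio, a scale on which no margin is defined. Followed as written, the named test gives no valid answer to the trial's single confirmatory question. The natural misreading, that no significant difference means non-inferior, carries a false-claim rate well above the planned 2.5%.

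**Working it through.** **Inputs.** From Sample-size calculation {14}: propofol success 79%, margin 0.10, one-sided alpha 0.025, power 0.80, 522 patients before and 576 after a 10% loss allowance (288 per group). Assumed: 79% success under remimazolam too. The article does not state this, but it reproduces the planned figure. The chi-square test is taken without continuity correction and the interval for the difference is the Wald interval.

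**1. The planned sample size.** n per arm = (1.96 + 0.8416)² × 2 × 0.79 × 0.21 / 0.10² = 260.4, so 261 per arm and 522 in total, as stated. Then 261 × 1.1 = 287.1, so 288 per arm and 576 in total, as stated. A two-sided equality test of 79% against 69% would need about 602 in total. The 522 therefore comes from a non-inferiority calculation, and the sizing and the named test address different hypotheses.

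**2. Chi-square test when remimazolam is exactly at the margin (79% against 69%).** The pooled rate is 0.74. The test is non-significant when the observed difference lies within 1.96 × SE₀, where SE₀ = √(2 × 0.74 × 0.26 / n). The true sampling error is SE₁ = √((0.79 × 0.21 + 0.69 × 0.31) / n).

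- n = 288: SE₀ = 0.03655, critical difference 0.0716, SE₁ = 0.03631. P(non-significant) = Φ((0.0716 − 0.10) / 0.03631) = Φ(−0.78) = 0.217.
- n = 261: SE₀ = 0.03840, critical difference 0.0753, SE₁ = 0.03815. P(non-significant) = Φ(−0.65) = 0.258.

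Exact calculation gives 0.215 and 0.257, and simulation agrees. A rule based on the 95% limit and the margin passes 0.025 of such trials.

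**3. Observed results at 288 per arm, propofol 228 successes (79.2%).**

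| Remimazolam successes | Difference (points) | Chi-square p | Lower 95% limit (points) | Non-inferiority |
|---|---|---|---|---|
| 228 | 0.0 | 1.00 | −6.6 | shown |
| 219 | −3.1 | 0.37 | −9.9 | shown |
| 218 | −3.5 | 0.32 | −10.3 | not shown |
| 210 | −6.3 | 0.079 | −13.2 | not shown |
| 208 | −6.9 | 0.052 | −13.9 | not shown |

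Every row reads as no significant difference. The non-inferiority conclusion changes between p = 0.37 and p = 0.32, nowhere near 0.05.

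**4. How often the two rules part.** If the true remimazolam rate is 74%, the chi-square is non-significant while non-inferiority is not shown in 41% of trials at 288 per arm (46% at 261). In the simulations a significant deficit never occurred together with a passed margin, so the harm lies in the non-significant result.

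**5. Power of the margin rule at 79% in both arms.** Power = Φ(0.10 / √(2 × 0.79 × 0.21 / n) − 1.96). For n = 261 this is Φ(0.845) = 0.801; for n = 288 it is Φ(0.986) = 0.838.

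**The case against.** The strongest reply is that the right estimate is already planned. The sentence after the chi-square test provides risk differences, the scale on which the margin is set, and calling the odds ratios secondary implies that the risk difference comes first. The sample-size section also ties a margin-based z-test to the primary outcome. On this reading the protocol needs one clarifying sentence, and the interval method or the order of superiority testing may sit in an analysis plan that is not shown.

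Much of this is fair. The planned estimate could carry the decision once a rule is attached. The choice of interval method is detail that an article may leave out. The two-sided convention is also numerically compatible with one-sided 0.025 if it is applied to a 95% interval; the fault is the null hypothesis, not the sidedness.

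It is also true that the 22–26% figure describes a misreading that the protocol does not prescribe, and that it depends on the version of the test: with continuity correction it would be 24% at 288 per arm and 29% at 261.

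The core is untouched. The article does not merely omit the rule: it names a test for the primary endpoint, and that test addresses the wrong hypothesis and differs from the one in its own sample-size section. The risk difference has no interval and no comparison with −10 points, and nothing says whether the adjusted or the unadjusted value decides.

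**Conclusion.** The concern holds and should be corrected before the data are analysed. The sample-size section and the analysis section specify different hypotheses, and the test named for the primary endpoint cannot support a non-inferiority claim.

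If a non-significant result were taken as non-inferiority, the false-claim rate at the margin would be about 22% at 288 per arm and 26% at 261, against 2.5% planned. Observed deficits of roughly 3.5 to 7 points would be reported as no difference although the interval reaches beyond −10 points.

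These figures assume 79% success under propofol, the uncorrected chi-square test and the Wald interval. The mismatch itself needs none of these assumptions.

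**What to change.** In Efficacy evaluation {20a}, replace the chi-square test as the primary analysis with a decision rule:

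- Non-inferiority is declared if the lower limit of the two-sided 95% confidence interval (equivalent to one-sided 0.025) for the risk difference in success, remimazolam minus propofol, lies above −10 percentage points.
- State whether the adjusted or the unadjusted risk difference decides, and name the interval method; a score-type or model-standardised interval would serve.
- Test superiority only after non-inferiority is met. The chi-square test, if kept, belongs there.
- In General principles {20a}, state that the two-sided p < 0.05 rule does not govern the primary non-inferiority decision.

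This costs wording and, under the article's own section {25}, ethics committee approval and an update of the online registration. It needs no new data and no more patients. Some results that would have read as no difference will be reported as non-inferiority not shown.
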